### Protocol

In the first visit, patients undergo spirometry, maximum voluntary isometric contraction (MIVC) and incremental cycle ergometer test, one hour apart. The isometric and dynamic endurance will be conducted in two visits each, totaling four visits (a week apart) with the subjects alternating between being in the test group and control group.

First, a venous blood sample will be taken from the patients. The isometric endurance test (IET) will be performed with 60% of MIVC. Then, patients will be randomized to receive either a placebo or LED application. Immediately after finishing this procedure, the patients will carry out the IET until the limit of tolerance or a fall of 20% strength is observed. After the test, another blood sample will be taken. During the next visit (one week later), the same order of procedures will be performed, except with the opposite application (LED or placebo) that was applied at Visits 2 and3.

For the dynamic endurance test (DET), the same procedures described above will be followed, except with 75% of the maximal workload obtained from incremental cycle ergometer test used instead of the IET. A summary of the protocol can be visualized in Figure 2.

**Figure 2 F2:**
[figure not shown]
Schematic representation of the isometric and dynamic protocols.

### Statistical analysis

The sample size was calculated based on the primary outcome, that is, endurance time. Assuming a Type 1 error rate of 0.05 and a Type 2 error rate of 0.2, with a magnitude difference of 55 sec at the dynamic endurance testing, a standard deviation of 79 sec [32], and a hypothetical drop-out rate of 10%, 35 patients with COPD would be needed to show statistically significant differences between LED and placebo in the endurance time. It will be used as the intention to treat analysis with the baseline data being used for missing data from patients who did not complete the whole protocol [33]. An additional analysis of the results involving only those patients who complete the treatment originally allocated will also be performed (per protocol analysis).

The normal distribution of data will be verified by the Kolmogorov-Smirnov test. The parametric data will be expressed by mean and standard deviation. The non-parametric data will be expressed by median and interquartile range. Differences in the variables of muscle function, exercise capacity and cardiorespiratory responses between the LED and placebo treatments will be compared with the paired Student’s *t*-test. Changes in median frequency and root mean square will be analyzed by repeated measures analysis of variance (basal, 25%, 50%, 75% and 100% of the endurance time) [34].

The linear regression analysis of the median frequency versus endurance time will be performed to obtain the slope coefficient of the straight line. For the correlations between the electromyographic variables (median frequency and root mean square) with endurance time, peak workload at cycling, and biochemical markers (CK, CRP and lactate). Pearson’s correlation will be used for normal distributions and Spearman’s correlation will be used for non-normal distributions. We used the GraphPad Software, Inc., GraphPadInStat™(version 2.0) La Jolla, CA, USAto calculate the sample size.

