**Methods:**

This study will assess 30 patients with moderate to severe obstruction (forced expiratory volume-one second,FEV_1_ ≤70% predicted). Isometric and dynamic protocols will be conducted in two visits each, for a total of four visits a week apart. First, venous blood will be taken from the patients. The isometric protocol will start with the determination of the maximum voluntary isometric contraction (MIVC) to determine the workload (60% of MIVC) for the isometric endurance test (IET). Patients will be randomized to receive either the placebo or LED application (each point will be irradiated for 30 s and the energy received at each point will be 41.7 J). Immediately after finishing this procedure, the patients will carry out the IET until the limit of tolerance or until a 20% fall of strength is observed. After the test, another blood draw will be taken. In another visit (one week later), the same order of procedures will be performed, except with the opposite (LED or placebo). For the dynamic endurance test (DET), the same procedures described above will be followed, except with 75% of the maximal workload obtained from the incremental cycle ergometer test used instead of the IET. The electromyography will be recorded during the isometric and dynamic protocols. Differences in muscle function, exercise capacity and cardiorespiratory responses between the LED and placebo applications will be analyzed. The therapeutic effects of LED could minimize muscle fatigue in patients with COPD by increasing exercise tolerance.

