### Outcome measures

The primary outcome for muscle function will be the endurance time (sec) on cycling. The secondary outcomes will be the slope coefficient from the regression line between the median frequency and endurance time, fatigue and dyspnea scores (from 0 to 10), and the levels of CK (U/L), CRP (mg/dl) and lactate (mmol/L). In addition, for the dynamic protocol, the maximum workload (watts), VO_2_ peak (L), ventilation (L), and heart rate (bpm) variables will also be analyzed.

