#### Dynamic endurance testing

For the dynamic endurance test (DET), the same procedures described above will be followed, except with 75% of the maximal workload obtained from incremental cycle ergometer test used instead of the IET. Patients will perform this test until the limit of tolerance (Tlim).

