#### Venous blood

Blood samples will be collected to measure the lactate levels, as well as the activity of CK and CRP. To measure these settings, a qualified nurse (blind to the group allocation) will perform the asepsis of ventral side of the arm. A blood sample will be collected prior to the application of the LED or placebo and immediately after ending the isometric endurance testing (Visits 1 and 2). The same procedure will be performed at Visits 3 and 4 prior to the application of the LED or placebo and after the cycle ergometer testing. The samples will be analyzed with infrared spectrophotometry via a spectrophotometer (FEMTO® Industry and Trade of Instruments, São Paulo, SP, Brazil) and specific kits for blood lactate analysis (Bioclin®, Belo Horizonte, Brazil) and CK analysis (Labtest®, Lagoa Santa, Brazil). PCR analysis will be carried out by the agglutination method using a specific analysis kit (Wiener Laboratories®, Rosario, Argentina).

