#### LED

Patients will receive a single application of LED or placebo on different days (a week apart). The LED or placebo will be administered immediately before the isometric and dynamic protocols. The radiation will be held stationary with slight pressure of the LED cluster (THOR Photomedicine®, London, UK) in contact with skin at an angle of 90°. The application will be performed on two points along the ventral side of the rectus femoris [31], one point on the greater prominence of the muscle belly of the vastuslateralis and vastusmedialis muscles. For the isometric exercise protocol, the application will be performed only on the right quadriceps femoris, while for the dynamic exercise protocol, both lower limbs will receive the application on the four sites for the quadriceps femoris, two sites for the hamstring muscle belly, and one site in the center of the triceps surae [18]. Each point will be irradiated for 30 s. The energy received at each point will be 41.7 J. The irradiation settings are summarized in Table 1.

**Table 1 T1:** Settings for LED cluster

Number of LEDs	69 (34 red LEDs and 35 infrared LEDs)
Wavelength	660 nm (red) and 850 nm (infrared)
Frequency	Continuous output
Optical output	10 mW (red) and 30 mW (infrared)
LED spot size	0.2 cm^2^ (for both), total spot sizes 13.8 cm^2^
Power density	0.05 W cm^-2^ (red) and 0.15 W cm^-2^ (infrared)
Energy	41.7 J (0.3 J from each red LED and 0.9 J from each infrared LED)
Energy density	1.5 J cm^-2^ (red) and 4.5 J cm^-2^ (infrared)
Treatment time	30 s per point, 120 s (total treatment time for isometric test), 420 s (total treatment time for dynamic test)
Number of irradiation points per muscle	4 points (isometric test) and 14 points (dynamic test)
Total energy delivered	166.8 J (isometric test), 583.8 J (dynamic test)
Application mode	Cluster held stationary to skin with slight pressure at a 90° angle

For the placebo, the same procedures will be performed but without irradiation. During the application of the LED or placebo, the patient will use protective glasses that make it impossible to see whether there is light being irradiated. This test will take approximately five minutes.

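### The intention-to-treat rule fills missing data with baseline values, but no baseline cycling endurance time, the primary outcome, is clearly described

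*Protocol article*

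**What the plan says.** All references are to the protocol article.

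- Statistical analysis: the main analysis is an "intention to treat analysis with the baseline data being used for missing data from patients who did not complete the whole protocol". LED and placebo are compared by paired t-test. A per-protocol analysis of completers is additional.
- Outcome measures: "The primary outcome for muscle function will be the endurance time (sec) on cycling".
- Dynamic endurance testing: this time comes from a test run like the isometric one, "except with 75% of the maximal workload obtained from incremental cycle ergometer test used instead of the IET", and continued to the limit of tolerance.
- Protocol, first visit: "In the first visit, patients undergo spirometry, maximum voluntary isometric contraction (MIVC) and incremental cycle ergometer test, one hour apart". No endurance test is listed.
- LED: "The LED or placebo will be administered immediately before the isometric and dynamic protocols".
- Abstract, Methods, after the application: "Immediately after finishing this procedure, the patients will carry out the IET until the limit of tolerance".
- Venous blood: "A blood sample will be collected prior to the application of the LED or placebo and immediately after ending the isometric endurance testing", with the same scheme at the dynamic visits.
- Protocol, a sentence that may point the other way: "The isometric endurance test (IET) will be performed with 60% of MIVC. Then, patients will be randomized to receive either a placebo or LED application".

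**The concern.** A rule that carries baseline data into missing cells needs a baseline measurement of the same quantity. For the outcome on which the trial is sized, the visit schedule does not clearly supply one. The analyst would have to leave the cell empty, so that the intention-to-treat analysis of the primary outcome becomes a completers analysis, or choose a stand-in from another test.

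In a crossover analysed by paired differences, a stand-in does not merely add noise. Placed in both periods, it forces that patient's difference to zero. Placed in one period, it sets a treated or placebo time against a different kind of measurement. The choice would fall to the analyst, possibly after the data are seen.

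The secondary outcomes have a milder form of the problem. Baseline values exist for several of them, but under conditions that differ from those of the missing value.

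**Working it through.** **1. The plan's own figure.** Inputs from Statistical analysis: difference 55 s, SD 79 s, type 1 error 0.05, type 2 error 0.2, drop-out 10%, stated total 35. Assuming a two-sided test and no within-patient correlation:

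n = 2 × [79 × (1.960 + 0.842) / 55]² = 2 × 16.19 = 32.4, so 33.

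Allowing for drop-out: 32.4 × 1.1 = 35.6; 32.4 / 0.9 = 36.0; 33 / 0.9 = 36.7, so 37. The stated 35 is within two patients of these. (With 79 s read as the SD of paired differences, the result is 17, or 19 with drop-out, which does not match.) The sample size does not decide this point, but it shows that 55 s and 10% are the plan's working values.

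**2. Which outcomes have a baseline?**

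- *Cycling endurance time:* none clearly described. The first-visit list has no constant-load test, and the abstract and the LED and Venous blood sections all fit one test per visit, after the application.
- *EMG and Borg scores:* EMG is recorded during the ramp (Surface electromyography recording) and Borg scores are taken at its end (Cardiopulmonary exercise testing). These are first-visit values, but from a ramp and not from an endurance test.
- *Peak workload and peak VO2:* first-visit ramp values exist.
- *Lactate, CK, CRP:* a pre-application sample exists. Used for a missing post-exercise value, it removes whatever change the exercise produced.

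**3. How many patients?** 0.10 × 35 = 3.5, so 3 to 4.

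**4. Same value in both periods.** Each such patient has a difference of zero. Expected mean difference = 0.9 × 55 + 0.1 × 0 = 49.5 s. In whole patients: 55 × 32/35 = 50.3 s with three, 55 × 31/35 = 48.7 s with four.

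**5. One period filled.** Let P be the mean placebo time, P + 55 the mean LED time and B the filled value, with 10% of patients affected.

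- LED visit missing: 0.9 × 55 + 0.1 × (B − P), a bias of 0.1 × (B − P − 55).
- Placebo visit missing: 0.9 × 55 + 0.1 × (P + 55 − B), a bias of 0.1 × (P − B).

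If B lies outside the range P to P + 55, the two biases have opposite signs. If it lies inside, neither is positive. An exactly even split of missed visits gives 49.5 + 0.05 × 55 = 52.25 s whatever B is, but with 3 to 4 patients an even split cannot be relied on. The document gives neither P nor B, so no size can be fixed.

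**6. Best case for the rule.** Suppose a true untreated endurance time existed and equalled the placebo mean (B = P). Then missing LED visits give 49.5 s and missing placebo visits give 55.0 s. Even a proper baseline is not neutral between the two conditions.

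**The case against.** **A baseline test may exist.** The Protocol section names the isometric endurance test before the randomisation step, and the dynamic test follows the same procedures. Read literally, this gives a pre-application endurance time. Figure 2, which might settle it, is not shown in the text available. A reader might infer that no baseline exists at all; the document does not support so flat a statement. What stands is that none is clearly described, that the abstract and the LED and Venous blood sections favour a single post-application test, and that the passages must be reconciled. On the literal reading, the baseline would be taken at the same visit as the outcome, so a patient who misses a visit misses that baseline too.

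**Other outcomes do have baselines.** This is correct. It would be wrong to say that no EMG or Borg baseline exists, since the ramp yields both. The objection to using them is comparability.

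**The analysis survives.** A reader might infer that the primary analysis set cannot be built. It can: it is all randomised patients. What is undefined is the value to insert for a few of them. The per-protocol analysis needs no insertion, so an interpretable comparison remains.

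**The bias may be large.** A reader might insert the ramp duration of 8 to 12 minutes and derive a bias of many seconds. The protocol never proposes that stand-in and gives no mean endurance time, so such figures would rest on assumption alone.

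**An article leaves detail to the full plan.** That is true of omissions. Here the article states a rule, and the rule does not fit the article's own schedule.

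**Conclusion.** The point holds for the primary outcome. The stated missing-data rule cannot be applied properly to cycling endurance time, because no baseline of that quantity is clearly described. For EMG, Borg scores and blood markers the rule can be run, but it inserts values from a different test or from before exercise.

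The calculable effect is modest: 55 s falls to about 49.5 s if the full 10% are filled with one value in both periods. With one period filled, the direction depends on the visit missed and the amount cannot be determined from the document. These figures assume that the 10% drop-out falls on the dynamic visits and that the true difference is 55 s. The lack of a clearly described baseline depends on neither assumption, but it does rest on reading the schedule as one post-application test per visit.

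**What to change.** - Delete the baseline-substitution rule.
- For endurance time, replace the paired t-test as the main analysis with a linear mixed model: treatment and period as fixed effects, patient as random effect, every observed post-application test included, valid under missing-at-random.
- Keep the paired analysis of patients with both dynamic visits as the per-protocol sensitivity analysis.
- Reconcile the Protocol sentence on the isometric test with the abstract and the LED and Venous blood sections, so that it is clear whether any endurance test precedes the application.
- State that patients lost before either dynamic visit contribute no endurance data, and report how many patients had none, one or both tests.

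**Cost.** A few sentences, standard software and no new measurements. Trial status says that recruitment is not yet open, so the change can be made before any data exist. There are two small downsides. The primary test is no longer the paired t-test. The model also cannot recover patients with no dynamic visit, which matters because the Venous blood section places the dynamic tests at Visits 3 and 4, after the isometric ones.

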#### Skeletal muscle function assessment

The strength of the quadriceps femoris will be obtained from the dominant leg by the maximal isometric voluntary contraction (MIVC). This measurement will be made with the patients seated on a leg extension chair (Carci®, São Paulo, Brazil) at 60° of knee flexion. A non-elastic strap connecting the ankle to a load cell (EMG System EMG800C, São José dos Campos, Brazil) will be interfaced to a computer to record the MIVC. The force will be expressed in Kgf. A strap will be placed across the patient’s pelvis to minimize hip movement during the tests. The patients will perform three repetitions of MIVC of the knee extensors, each one maintained for five seconds, with a one minute rest between them. The highest value from the three reproducible contractions (<5% variability among attempts) will be considered for analysis, when the difference in strength of three contractions exceeds 5%, another measure of MIVC will be requested. The greatest value of these three contractions will be considered as the MIVC [22]. After a resting period of five minutes, the IET of the quadriceps femoris will be evaluated by the isometric endurance time at 60% of the MIVC until the limit of tolerance (Tlim). The isometric endurance test will be finished when a 20% drop of the produced force occurs. All measurements will be performed with visual feedback on the computer screen [22]. Dyspnea and leg fatigue will be evaluated before and immediately after the test by the modified Borg scale [23]. This test will take approximately 15 minutes.

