#### Surface electromyography recording

Surface electromyography (sEMG) signals will be recorded (EMG System, model EMG800C, Sao José dos Campos, Brazil) during the MIVC, isometric endurance test, and the incremental cycle ergometer test. The sEMG signals will be recorded with a preamplifier (gain 1,000x) and common mode rejection of more than −85 dB. The participants’ skin will be prepared before the placement of the EMG electrodes by shaving the hair at the site of the electrode placement and cleaning the skin with alcohol [24].

Bipolar passive disposable dual Ag/AgCl snap electrodes with a 1-cm diameter for each circular conductive area and a 2-cm center-to-center spacing will be placed over the longitudinal axes of the vastuslateralis. They will be placed in the direction of the muscle fiber, taking as reference two-thirds of the distance between the anterior superior iliac spine and the lateral edge of the patella [24]. Finally, a ground electrode will be put on the left elbow.

The sampling frequency will be 2,000 Hz [25] and the criterion adopted to normalize the EMG data will be the MIVC. The digitized EMG data will first be band-pass filtered at 20 to 400 Hz using a fourth order Butterworth filter with a zero lag. For the temporal analysis, the amplitude of the EMG signals will be expressed as root mean square (RMS) (1-s moving window) and normalized by MIVC [26]. For the time-frequency analysis, the EMG data will be analyzed with a short-time Fourier transform applied to 1-s epochs [27]. The median frequency of the spectrum for each epoch will be computed, and the linear regression of the median frequencies versus time will be determined. The slope of the straight line (indicating the rate of frequency change per second) will be adopted as a second index of fatigue [28-30]. All data were analyzed using a customized program written in Matlab (Mathworks Inc., Torrance, California, EUA).

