#### Cardiopulmonary exercise testing

The maximal incremental cycle ergometer test will be carried out on an electromagnetically braked cycle ergometer (Corival, LODE B.V. Medical Technology, Groningen, The Netherlands) with gas exchange and ventilatory variables being analyzed breath-by-breath (Medical Graphics Corporation (MGC), St. Paul, MN, USA). After 2 minutes at rest and more than 2 minutes with a real “zero” workload obtained by a system that moves the ergometer flywheel, the power (W) will be continuously increased in a linear “ramp” pattern (5 to 15 W min^-1^) so that the incremental exercise test duration will be between 8 and 12 minutes [29]. The following data will be obtained breath-by-breath: pulmonary oxygen uptake (VO_2_, mL min^-1^), pulmonary carbon dioxide production (VCO_2_, mL min^-1^), minute ventilation (VE, L min^-1^), tidal volume (VT, mL), respiratory rate (f, respirations per minute); ventilatory equivalent for O_2_ and CO_2_ (VE/VO_2_ and VE/VCO_2,_ respectively), and end tidal partial pressures of O_2_ and CO_2_ (PETO_2_ and PETCO_2_, mmHg). ECG tracings and heart rate (HR) will be recorded continuously and oxygen pulse (VO_2_/HR) will be calculated. Arterial oxygen saturation (SpO_2_) will be measured by pulse oximetry. Blood pressure (BP) will be measured during every two minutes of exercise. The average VO_2_ for the last 15 s of the ramp will be considered representative of the subject’s peak VO_2_. Subjects will be asked to rate dyspnea and leg fatigue at exercise cessation by using the modified Borg scale [23]. This test will take approximately 30 minutes.

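### EMG compared at percentages of each test's own length, and Borg scores taken only at the ends, can miss slower fatigue or suggest extra fatigue if LED lengthens the test

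*Protocol article*

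**What the plan says.** The Outcome measures section fixes the primary endpoint: "The primary outcome for muscle function will be the endurance time (sec) on cycling". It then names the EMG slope and the Borg scores, which have a maximum of 10, among the secondary outcomes: "The secondary outcomes will be the slope coefficient from the regression line between the median frequency and endurance time, fatigue and dyspnea scores (from 0".

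The Statistical analysis section says that changes in median frequency and RMS "will be analyzed by repeated measures analysis of variance (basal, 25%, 50%, 75% and 100% of the endurance time"). The sentence lists time levels and mentions neither LED nor placebo. The sentence before it says that differences in the muscle, exercise-capacity and cardiorespiratory variables "between the LED and placebo treatments will be compared with the paired Student’s" t-test. It does not connect that test to the ANOVA.

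The Surface electromyography recording section puts the slope on absolute time: "The slope of the straight line (indicating the rate of frequency change per second) will be adopted as a second index of fatigue".

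For symptoms in the isometric test, the Skeletal muscle function assessment section says: "Dyspnea and leg fatigue will be evaluated before and immediately after the test by the modified Borg scale". For the incremental cycle test, the Cardiopulmonary exercise testing section says: "Subjects will be asked to rate dyspnea and leg fatigue at exercise cessation by using the modified Borg scale". The Dynamic endurance testing section gives no symptom timing of its own. It refers back to the procedures already described and adds: "Patients will perform this test until the limit of tolerance (Tlim"). The isometric test runs to the limit of tolerance or a 20% fall in force.

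**The concern.** When a test ends at tolerance, its length is itself an outcome. A time point set at 50% of the test's own length is then a different number of seconds in the two conditions whenever LED changes endurance. The trial's hypothesis is that it does. A score taken at the end has the same weakness, because each condition is measured when the patient stops, whenever that is.

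At stake is the interpretation of the secondary fatigue measures. If LED slows fatigue and patients simply reach the same end state later, the percentage curves and the end scores can coincide and be reported as no effect. If LED leaves the rate unchanged and patients only continue for longer, the late points can look worse under LED. Either result could be read as evidence against the proposed mechanism when it comes from the time scale.

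**Working it through.** **Inputs.** From the Statistical analysis section: an expected difference of 55 s in the dynamic test, an SD of 79 s, and 35 patients with 10% drop-out. The article states no figure for this point that could be reproduced. It gives no endurance time under placebo, so T0 = 120 to 400 s is assumed, with T1 = T0 + 55 under LED. Also assumed: a linear change from the start value F0, with a total fall D in the placebo test.

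**Misalignment.** The 25, 50, 75 and 100% points fall 0.25, 0.50, 0.75 and 1.00 × 55 = 14, 28, 41 and 55 s later under LED.

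**Case A: LED slows the decline and both tests end at the same value.** At fraction p both curves equal F0 − pD, so the percentage-scale difference is exactly 0 at every point. At equal absolute time T0 the difference is D(1 − T0/T1).

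**Case B: same fall per second, LED only lengthens the test.** At equal absolute time the difference is 0. At the 100% point LED looks worse by D × 55/T0.

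| T0 (s) | T1 (s) | A: percentage scale | A: equal time T0 | B: 100% point | B: equal time |
|---|---|---|---|---|---|
| 120 | 175 | 0 | 31% of D | 46% of D worse | 0 |
| 180 | 235 | 0 | 23% | 31% worse | 0 |
| 240 | 295 | 0 | 19% | 23% worse | 0 |
| 300 | 355 | 0 | 15% | 18% worse | 0 |
| 400 | 455 | 0 | 12% | 14% worse | 0 |

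**Between the cases.** Let the decline per second under LED be r times that under placebo. The percentage-scale difference at fraction p is pD(1 − r × T1/T0), whereas at equal time T0 it is D(1 − r). With T0 = 300 s and r = 0.9, the 100% point gives D(1 − 0.9 × 355/300) = −0.065D. LED looks 6.5% of D worse although its decline is 10% slower. The same algebra holds for any measure that changes roughly linearly with time, RMS included.

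**Simulation, for illustration.** 3,000 simulated trials of 31 completers (35 × 0.9 = 31.5, rounded down). Assumed: placebo endurance with SD 60 s; LED difference with mean 55 s and SD 79 s, read as the SD of paired differences; median-frequency fall of 15 Hz (SD 3); measurement error SD 3 Hz. Share of trials with p < 0.05 by paired t-test, for T0 = 180 / 240 / 300 s:

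| Comparison | Case A (true slowing) | Case B (rate unchanged) |
|---|---|---|
| 50% point | 5.7 / 4.8 / 4.5% | 71.2 / 49.6 / 37.9% |
| 100% point | 4.6 / 5.4 / 5.0% | 91.2 / 82.9 / 73.4% |
| Equal absolute time | 63.8 / 55.3 / 48.5% | 5.3 / 5.1 / 5.1% |
| Slope per second | 37.5 / 35.8 / 37.5% | 5.4 / 4.8 / 5.1% |
| Endurance time | 98.2 / 96.6 / 95.3% | 98.2 / 96.3 / 96.8% |

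The percentage points have no power in Case A and mostly mislead in Case B. Equal-time values and the slope behave correctly in both.

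**The case against.** The strongest reply is that the plan already has an absolute-time fatigue measure. The median-frequency slope is a named secondary outcome in change per second. In the 300 s example of Case A it would come out 15% shallower under LED. Endurance time, the primary outcome, records a delayed end state directly. Both points stand. A reader might infer that all the EMG analysis hides the effect; the documents do not support that. RMS, however, has no slope or other absolute-time index, and neither do the Borg scores.

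A reader might also infer that the ANOVA excludes treatment and tests change over time only. The parenthesis lists time levels in a condensed article, and the preceding sentence does plan an LED-placebo comparison. The model may be completed in an analysis plan that is not shown, so the missing term is a matter to make explicit and not a demonstrated error. The percentage time scale, by contrast, is written down.

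A third tempting reading is that oxygen uptake, ventilation and heart rate in the endurance test are compared only at the end. No section says so. Gas exchange is recorded breath by breath and heart rate continuously, as described for the incremental test.

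Finally, nothing in the article says that patients stop at equal symptom levels. The isometric test can also end on the force criterion, which does not force equal Borg scores. The Borg statement for cycling is written for the incremental test and reaches the endurance test only by cross-reference. These points limit the symptom argument to what can happen. They do not supply a rating during exercise.

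**Conclusion.** The point holds for a limited set of secondary comparisons: the repeated-measures ANOVA of median frequency and RMS, and the Borg scores. The Borg scores are not part of that ANOVA; theirs is a parallel problem of timing. If LED lengthens the test, these comparisons can miss a slower rate of fatigue or suggest more fatigue at an unchanged rate. They need not do so, since the result depends on how the end values compare.

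The zero difference in Case A is algebraic, given a linear change and equal end values. The other sizes rest on the assumed placebo endurance of 120 to 400 s, and the rejection rates on assumed EMG values. The 55 s applies to cycling only; the article gives no expected difference for the isometric test. The primary outcome, the median-frequency slope and the sample size are unaffected. The change is worth making before recruitment, which the Trial status section says has not opened, because symptom ratings not taken during exercise cannot be recovered later.

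**What to change.** - **Add isotime comparisons.** Compare RMS and median frequency, and in the cycling endurance test oxygen uptake, ventilation and heart rate, at the same absolute times in both conditions, up to the end of the patient's shorter test.
- **State the test of LED.** Use a model with treatment, time, treatment-by-time and period, with patient as a random effect. The treatment and interaction terms are the tests of LED.
- **Keep the existing values as description.** Percentage-of-own-length and end-of-test results stay in the report but do not carry the inference on fatigue rate. The slope per second stays as planned.
- **Where feasible, record Borg at fixed times** during the cycling endurance test as well as at the end.

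The cost is some analysis wording and a few extra ratings per cycling test. The analysis part needs no new measurements, provided that EMG, gas exchange and heart rate are recorded in the endurance test. The abstract says this for EMG, but the EMG recording section names the incremental test; for the others it follows from the cross-reference to earlier procedures. One sentence should confirm it. Lactate is drawn only before application and after the test, so this change does not cover it.
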